### Recruitment

All patients in the ED should be contacted as early as possible during the enrollment process by a project employee who informs both verbally and in writing about the project. If the 4 hour requirement is an obstacle for receiving the expected number of inclusions, the steering committee might waive this criterion. The patient is allowed to have a family member, friend or acquaintance, as a lay representative present at the information.

The project employee will have a healthcare background (nurse or medical student) and is employed by the department.

Privacy will be secured during the information and no treatment must be delayed because of the enrolment.

All patients are offered up to 1 hour’s consideration time before written consent is obtained. The consent includes that the project employee is allowed to obtain a swab from pharynx, nose and rectum, that the microbiological analysis and the exposure information is used for a scientific purpose, and that information concerning antibiotic consumption from the patient records is registered. The patient also receives information about who he/she can contact afterwards for additional questions.

### Data collection methods

#### Interview

The project staff in the emergency department collects information about the background and possible risk factors for carrier status through an interview with the patient. The questions included are prepared on the basis of the Danish National Board of Health’s guidance on preventing spreading of MRSA [9].

#### Collection of swabs

The patient is swabbed in the nose (ESwab (Copan, SSI Diagnostica, Hillerød, Denmark)), throat (ESwab) and rectum (FecalSwab (Copan)).

Nasal swabs are obtained by inserting a swab into the anterior nares and rotating it along the mucous membrane. Throat swabs are collected by rubbing a swab along the mucosal surfaces of the tonsils and pharynx. These samples are already collected routinely in Denmark in selected patients who are screened for MRSA, according to the guidelines of the National board of Health.

Rectal swabs are obtained by inserting a swab 1–2 cm. into the anal canal and rotate it against the mucosal surface a few times. The procedure is comparable to a temperature measurement in the rectum.

The three swabs are labeled with barcodes containing information on project department and a unique project running number. All samples are sent to the regional department of clinical microbiology using the same transport arrangements as for routine tests.

#### Microbiological analysis

The collected samples are examined at the Departments of Clinical Microbiology at Aalborg University Hospital, Aarhus University Hospital, Odense University Hospital and Slagelse Hospital. The same method of analysis is applied to all four departments.

Nose and throat swabs are examined for the presence of MRSA: An enhancement broth [Tryptic soy broth supplemented with 2,5% NaCl, 3,5 mg/L cefoxitin and 20 mg/L aztreonam (Herlev Hospital, Herlev, Denmark)] is inoculated with 100 μL from both ESwab media and incubated at 35–37 °C for 16–24 h. Subsequently, a selective chromogenic medium [CHROMagar MRSA II agar (Becton Dickinson, Heidelberg, Germany)] is inoculated with 100 μL of the enhancement broth and incubated for an additional 42–48 h in atmospheric conditions. Possible isolates of *Staphylococcus aureus* are identified by mass spectrometry [(MALDI-TOF-MS: BioTyper/Bruker (Bruker Daltronics, Bremen, Germany) or Vitek MS (bioMérieux, Marcy-l’Etoile, France)] and screened for cefoxitin resistance according to the European Committee on Antimicrobial Susceptibility Testing (EUCAST, eucast.org) and for the presence of the *mecA*-gene by polymerase chain reaction (PCR). *mecA*-negative, cefoxitin resistant isolates are examined for the presence of the *mecC*-gene.

Rectum swabs are examined for the presence of VRE, ESBL, CPE and CD. VRE: 100 μL of the FecalSwab medium are transferred to an enhancement broth [Brain Heart Infusion Broth supplemented with vancomycin 4 mg/L and 60 mg/L aztreonam (Herlev Hospital)]. The enhancement broth is incubated at 35–37 °C for 16–24 h and 100 μL of the broth are subsequently transferred to a selective chromogenic medium [chromID VRE Agar (bioMérieux)] and incubated for further 42–48 h in atmospheric conditions. Possible isolates of *Enterococcus spp* are identified by MALDI-TOF-MS and all confirmed *Enterococcus spp* isolates are examined for the presence of the *vanA-* and *vanB*-gene by PCR. ESBL, CPE and CD: Three different selective chomogenic substrates [ESBL: CHROMagar ESBL bi-agar (Becton Dickinson), CPE: chromID CARBA SMART agar (bioMérieux) and CD: chromID C.difficile agar (bioMérieux)] are each inoculated with 100 μL of the FecalSwab medium and incubated at 35–37 °C under atmospheric conditions for 18–24 h (ESBL and CPE) or in an anaerobic atmosphere for 42–48 h (CD). Suspected isolates of *Enterobacteriaceae* (ESBL or CPE) or CD are identified by MALDI-TOF-MS. Possible ESBL isolates are phenotypically characterized according to EUCAST using the ROSCO Total ESBL Confirm Kit (ROSCO, Taastrup, Denmark). Possible CPE isolates are screened for meropenem susceptibility according to EUCAST and stored for later genotypic characterization. Possible CD isolates are examined for the presence of toxin A (*tcdA-*gene)*,* toxin B (*tcdB-*gene) and binary-toxin (*cdtA*-gene) by PCR*.* Binary-toxin positive CD isolates will be examined for genotypic markers for CD ribotype 027.

All obtained isolates of cefoxitin-resistant *Staphylococcus aureus*, *Enterococcus spp*, cefalosporin- and/or meropenem-resistant *Enterobacteriaceae* and *Clostridium difficile* will be stored at − 80 °C.

### Data collection, management, and analysis

#### Data entry

All patients will be provided with project running number, which will be used throughout the project in the interviews and processing of microbiological samples to secure anonymity. An ID file with the project running number and the personal registration number (PRN) number will allow tracing the patient information concerning use of antibiotics before the admission in the national medicine registries, and for returning test answers to those patients who requested this information.

The answers from the interviews are entered directly to an electronic questionnaire (SurveyXact®, Rambøll, Aarhus, Denmark) on tablet PCs used solely for the project. Data is transmitted directly to the central secured data file storage.

The microbiological samples are analyzed anonymously using project running numbers and microbiological data are recorded in the local laboratory information system [Aarhus, Odense and Slagelse: MADS (Aarhus University Hospital, Aarhus, Denmark [www.madsonline.dk]) and Aalborg: ADBact (Autonik Ab, Sweden)]. Data is extracted from these databases after the end of the study to the central database where the results are merged to the interview information. The results will not appear in the patients hospital file.

Microbiological test results are merged with the interview data using the project running number and data from the medicine registries are merged with the data set by using the PRN number.

After data cleansing and validation the final data file will be anonymized before data analysis.

Information concerning antibiotic treatment before the admission will be obtained from National Board of Health, medicine registries.

The data analyzes are conducted in STATA 14 in cooperation with a statistician.

The prevalence of the resistant bacteria are calculated at hospital level, regional level and national level and described with relation to residency (region and degree of urbanization), sex, age and risk factors.

In one part of the national aggregated data set, a screening model for identification of carrier stage of resistant bacteria is developed, based on the interview and medicine information. The model is then validated in another part of the dataset. The model building is based on the individual resistant bacteria, and includes univariate and multivariate logistic regression. Relevant indicators from well-defined domains are selected, tested for correlations and interactions as well as goodness of fit of the final model.

Non-participant analysis is performed. For missing data multiple imputation is used.

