### Outcomes

The primary outcome is the presence of MRB (MRSA, ESBL, VRE, CPE) and CD in patients in the ED, expressed as prevalence (proportion) in percentage on admission among the included patients.

The secondary outcomes are the information on admission concerning risk factors for carriage of antibiotic resistant bacteria, expressed as the proportion and odds ratios between patients with and without MRB (Table 1).

**Table 1 Tab1:** Variables examined in the study

Examined risk factors for carrying resistant bacteria	-Travel activity last year -Work/stay at hospital, nursing home, schools, prison, military, asylum center/refugee camp, hostel, daycare or war zone in and outside the Nordic region. -Signs of infections, shared sports equipment, tattoos/piercings -Contact with mink farm, live pigs, cattle or poultry -Hospitalized for the past six months -Invasive surgery performed at a foreign clinic/hospital -Drainage tubes, indwelling catheters, nutrition tubes, ulcers, abscesses, eczema, chronic skin disorders or IV drug abuse within the last six months -Antibiotic treatment within the last 6 months -Previously carrier of resistant bacteria, household-like contact with carrier or worked/stayed in places with known transmission of resistant bacteria
Outcome variables	-MRSA: methicillin resistant *Staphyloccus aureus* -ESBL: extended-spectrum beta-lactamase producing enterobacteria -VRE: vancomycin resistant enterococci (VRE) -CPE: carbapenem resistant enterobacteria -CD: *Clostridium difficile*

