### Sample size

A Danish study showed an MRSA occurrence of 0.9% in an ED [8]. It is assumed that VRE and CPE have a lower occurrence and ESBL and CD a higher occurrence [2]. With the funding obtained, 1.325 patients can be included per ED, corresponding to 2650 patient in each region and 10.600 patients in total. The true frequencies of the prevalence of resistant bacteria with 95% confidence, based on expected prevalence of resistant bacteria of 0.5%, 1%, 10% and 25% is shown in Table 2 for different samples sizes (anticipated admission rate of 10.000 patients/year).

**Table 2 Tab2:** Sample size calculation for prevalence (source Openepi.com)

Calculations of sample size estimates 95% limits of confidence								
	sample size (number of patients)							
	600	1100	1500	1750	2200	3500	5000	10,000
Anticipated prevalence of resistant bacteria	95% limits of confidence (+/− % of prevalence)							
0.5%	+/− 0.5	+/− 0.4	+/− 0.35	+/− 0.30	+/− 0.25	+/− 0.20	+/− 0.14	+/− 0.03
1%	+/− 0.8	+/− 0.55	+/− 0.45	+/− 0.40	+/− 0.35	+/− 0.30	+/− 0.20	+/− 0.05
10%	+/− 2.5	+/− 1.75	+/− 1.4	+/− 1.25	+/− 1.2	+/− 1.0	+/− 0.6	+/− 0.2
25%	+/− 3.5	+/− 2.5	+/− 2.0	+/− 1.75	+/− 1.70	+/− 1.45	+/− 0.9	+/− 0.2
	Example: at a prevalence of for instance MRSA of 0.5% the 95% limits of confidence with a sample size of 1.100 patient is +/0.4%, which means that the prevalence with 95% certainty is from 0.1–0.9%.							

Assumptions: 10.000 patients pr year, 95% confidence limits

For the analysis of risk factors for carrier stage of resistant bacteria, only calculations at national level will be performed.

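### Separate logistic models per organism are planned on part of the data, but VRE and CPE may have too few carriers to fit them, and the MRSA model risks overfitting unless candidates are cut hard first

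*Protocol article*

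**What the plan says.** The objectives in the protocol article include identifying risk factors for each of MRSA, ESBL, VRE, CPE and CD, and building screening tools from them. Odds ratios comparing patients with and without resistant bacteria are part of the secondary outcomes.

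The end of the Data entry section sets out the modelling: "The model building is based on the individual resistant bacteria, and includes univariate and multivariate logistic regression". Only some of the data are used for development: "In one part of the national aggregated data set, a screening model for identification of carrier stage of resistant bacteria is developed". The rest serves another purpose: "The model is then validated in another part of the dataset". The split share is not given. The same section says that indicators are chosen from domains, that correlations and interactions are tested, and that the fit of the final model is checked. It does not say how many indicators are kept or whether the outcome guides the choice.

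The Sample size section gives the numbers available: "With the funding obtained, 1.325 patients can be included per ED, corresponding to 2650 patient in each region and 10.600 patients in total". On prevalence it says: "A Danish study showed an MRSA occurrence of 0.9% in an ED", and then: "It is assumed that VRE and CPE have a lower occurrence and ESBL and CD a higher occurrence". The lowest prevalence in Table 2 is 0.5%. Table 2 concerns only the precision of a prevalence. For risk factors, the section fixes only that the analysis is national.

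Table 1, in the row "Examined risk factors for carrying resistant bacteria", lists the exposures in nine groups.

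**The concern.** In a logistic model the information comes mainly from the rarer outcome class, here the carriers, and not from the 10,600 patients. The protocol ties its sample size to prevalence precision, yet commits to a separate model for each organism on a subset of the data. No passage relates the number of carriers to the number of candidate predictors.

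Two things can go wrong when carriers are few:

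- An exposure with no exposed carrier has no finite maximum-likelihood log odds ratio. Several Table 1 items are plausibly uncommon, such as prison, war zone, mink farm or surgery abroad.
- Where estimates are finite, coefficients tend to be too extreme, and the tool separates carriers from non-carriers less well in new patients than in the development data.

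At stake are the reported odds ratios for the rarer organisms and the credibility of any screening tool built from them. The Discussion expects that tool to inform antibiotic treatment and infection control.

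**Working it through.** **Inputs from the protocol article**

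- Sample size: 1,325 × 8 departments = 10,600, and 2,650 × 4 regions = 10,600. The stated total is reproduced.
- MRSA prevalence: 0.9% (Sample size).
- Exposures in Table 1, by group: 1 travel + 9 places + 3 (infection signs, sports equipment, tattoos/piercings) + 4 animal contacts + 1 hospitalisation + 1 surgery abroad + 8 devices, skin conditions and IV drug use + 1 antibiotics + 3 carrier contact = 31. Splitting the 9 places into inside and outside the Nordic region adds 9, giving 40. Age, sex, region and urbanization are not counted.

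**Assumptions, because the document gives no figure**

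- VRE and CPE prevalence: 0.1% to 0.5%.
- ESBL and CD prevalence: 5%, for illustration.
- Development share: one half, with two thirds as an alternative.
- Nine variables, one per Table 1 group, as a generous reading of the domain step.

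**Expected carriers** = 10,600 × prevalence × share

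| Prevalence | All data | Two thirds | Half |
|---|---|---|---|
| 0.9% (MRSA) | 95.4 | 63.6 | 47.7 |
| 0.5% | 53.0 | 35.3 | 26.5 |
| 0.1% | 10.6 | 7.1 | 5.3 |
| 5% | 530 | 353 | 265 |

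**Carriers per candidate variable** = carriers / variables

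| Prevalence | 9 variables: all data | 9 variables: two thirds | 9 variables: half | 31 to 40 variables: half |
|---|---|---|---|---|
| 0.9% (MRSA) | 10.6 | 7.1 | 5.3 | 1.5 to 1.2 |
| 0.5% | 5.9 | 3.9 | 2.9 | 0.9 to 0.7 |
| 0.1% | 1.2 | 0.8 | 0.6 | 0.2 to 0.1 |
| 5% | 58.9 | 39.3 | 29.4 | 8.5 to 6.6 |

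**Empty cells.** For an exposure of frequency q unrelated to carriage, the probability that none of c carriers is exposed is (1 − q)^c.

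- MRSA, half split, q = 1%: 0.99^48 = 0.62.
- 0.5% prevalence, half split, q = 1%: 0.99^27 = 0.76.
- 0.1% prevalence, half split, q = 10%: 0.90^5 = 0.59.

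The probabilities are lower for exposures that raise the risk of carriage.

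**Expected shrinkage as a cross-check.** S = 1 − k / (−n ln(1 − R²)), where k is the number of parameters, n the development size and R² the Cox-Snell value. The Cox-Snell value is taken as 10% to 15% of its maximum, that is, an assumed Nagelkerke R² of 0.10 to 0.15. A usual target is S = 0.9.

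MRSA in a half (n = 5,300): the maximum Cox-Snell R² at 0.9% is 0.0976. At Nagelkerke 0.10, R² = 0.00976 and −n ln(1 − R²) = 52.0.

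- k = 9: S = 1 − 9/52.0 = 0.83.
- k = 40: S = 1 − 40/52.0 = 0.23.

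Over the whole assumed R² range in a half split:

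| Prevalence | S with 9 variables | S with 31 to 40 variables |
|---|---|---|
| 0.9% (MRSA) | 0.83 to 0.88 | 0.23 to 0.60 |
| 0.5% | 0.72 to 0.82 | −0.23 to 0.36 |
| 0.1% | −0.08 to 0.28 | below 0 |

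A value near or below zero means that the data cannot support the model.

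**The case against.** The strongest reply is that the document never says 31 or 40 predictors enter a model. Table 1 lists what is examined, and the domain step is a form of data reduction. This stands, and it matters most for MRSA: with nine variables the expected shrinkage in a half split is 0.83 to 0.88, not far below the usual target. A reader might infer that the MRSA model is bound to be overfitted, but the text does not support that.

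A reader might also infer a univariate significance filter followed by an unpenalised multivariable fit. The text says only that model building includes both kinds of regression. It states no order, no threshold and no estimator, and the univariate odds ratios may simply be descriptive. Criticism of a filter is therefore not part of this point.

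A handful of VRE or CPE carriers is likewise an assumption. The document says only that they are less common than MRSA, and at 0.5% there would be 53.

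The choice of estimator is often left to an analysis plan, and a statistician is to be involved. That covers silence on detail. It does not cover the commitments this article does make: a separate model and tool for each organism, developed on a part of the data, with expected counts that remain low after a generous reduction of candidates.

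Lastly, the separate validation part could reveal optimism. It would not correct it, and for the rarer organisms it would itself rest on few carriers. Goodness of fit in the development data does not reveal overfitting.

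**Conclusion.** The concern holds in graded form.

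- **VRE and CPE:** if prevalence is well below 0.5%, multivariable maximum-likelihood models are likely to be unstable or not estimable. At 0.1%, a half split leaves about 5 carriers, or 0.6 per variable with nine variables. At 0.5% it leaves about 27, or 2.9 per variable, which is still thin.
- **MRSA:** the model is at risk of overfitting. The degree runs from moderate (about 5 carriers per variable with nine variables) to severe (1.2 to 1.5 with the full Table 1 list), depending on how far candidates are cut without using the outcome.
- **ESBL and CD:** probably adequate, at about 530 carriers each under the assumed 5%.

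Only the MRSA prevalence, the total sample size and the Table 1 list come from the document. The VRE, CPE, ESBL and CD prevalences, the split share, the nine-variable reduction and the R² range are assumptions. A larger development share eases the figures but does not change the conclusion for VRE and CPE: at two thirds, nine variables give 3.9 carriers per variable at 0.5% and 0.8 at 0.1%.

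**What to change.** For MRSA, VRE and CPE, amend the modelling paragraph before the analysis as follows:

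1. Reduce the candidates by domain from subject knowledge and exposure frequency, without reference to carrier status, and list them in advance.
2. Fit the screening model by penalised logistic regression (ridge or lasso).
3. Report Firth or exact odds ratios for risk factors.
4. Make multivariable models and tools for VRE and CPE conditional on the number of carriers observed in the development data relative to the number of candidate parameters. Otherwise report univariable Firth or exact odds ratios only.

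ESBL and CD can follow the existing plan.

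The cost is plan wording and standard software, with no extra patients or data. The downsides are that shrunken estimates are less familiar to readers and that VRE and CPE may end without a screening tool, which should be stated openly against the fourth objective.

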#### Monitoring

The daily inclusion of participants will be monitored by the steering committee and the numbers of inclusion will be instantly available for all the included centers on a home page.

No interim analysis will be made. The primary analysis of data will be performed by three members of the steering committee after the last patient has been included and all the microbiological analysis finalized. The results will be discussed and evaluated first in the steering committee and afterwards with all the included departments.

#### Protocol amendments

Important protocol modifications like changes in eligibility criteria or outcome will be communicated to the relevant parties, i.e. sponsor, trial registry and scientific ethical committee.

#### Confidentiality

The test material will be destroyed immediately after the sample has been analyzed. Bacterial isolates are stored for further characteristics.

All personal information and project samples are anonymized throughout the study process using a project ID running numbers and the results cannot be seen in the patient file or made available for the clinical care providers. The results of the final analysis are expected to be available only 4–6 months after the index hospitalization. A key file will be created that connects the project ID serial number with the patient’s civil registration number. It allows for further future analyzes and is necessary for any feedback to the included patients. The PRN key is registered in the registration form, which is saved on secured drive.

#### Access to data

Only the members of the steering committee will have access to the final trial dataset. Other researches may be granted access to the anonymized data for analysis on reasonable request to the corresponding author.

#### Ancillary and post-trial care

The data files will be handed to the Danish National Archieves upon completion of the study.

#### Dissemination policy

The results of the project will be presented in English in peer-reviewed articles in recognized scientific journals. A report is also prepared for use by the National Board of Health, including an overall assessment of the results and clinical implications, deviations between expected and actual results and achieved experience in the project.

The results of the project will also be disseminated through participation in academic and other conferences, as well as through the printed and electronic press.

The author panel for both scientific articles and the report to the Health Board will include the steering committee and one local researcher from each of the participating emergency departments and clinical microbiology departments in accordance with the Vancouver criteria. No professional writers will be used.

Positive, negative and inconclusive results will be published.

## Discussion

The study will provide the prevalence of colonized patients with resistant bacteria on arrival to the ED and variation in demographic patterns, and will develop a clinical tool to identify certain risk groups. This will enable the clinician to target antibiotic treatments and to reduce the in-hospital spreading of resistant bacteria. This knowledge is important for implementing and evaluating antimicrobial stewardships, screening and infection control strategies.

